10.2.2. Definition of Serious Adverse Events

A serious adverse event (SAE) is any untoward medical occurrence, regardless of dose, that meets any of the following criteria.

a. Resulting in death.

b. Life-threatening.

"Life-threatening" means that, at the time the event occurred, the subject was at risk of death; it does not imply a hypothetical situation in which a more severe manifestation of the event might have caused death.

c. Events that require hospitalization or prolongation of an existing hospitalization for treatment.

- ✓ In general, hospitalization refers to the subject staying in a hospital or emergency department (typically overnight or longer) to receive observation and/or treatment that cannot be appropriately performed in a clinic or outpatient setting. Complications that arise during hospitalization are considered adverse events; if the complication results in an extension of the hospital stay, or if the complication itself meets another SAE criterion, it shall be classified as an SAE.
- ✓ Hospitalization for treatment of a comorbidity that has not worsened since the start of the clinical trial, hospitalization for administration of the investigational product, hospitalization for examinations, or hospitalization intended to reduce the burden on

subjects traveling from distant locations shall not be considered a SAE.

d. Results in persistence or significant disability or incapacity.

- ✓ Refers to a condition that markedly impairs the subject's normal daily functioning.
- ✓ Medical events that are not of substantial importance, such as headache, nausea, vomiting, diarrhea, influenza, or minor injuries (e.g., ankle sprain) without accompanying complications, are excluded.

e. Congenital anomaly or birth defect.

f. Other medically important conditions:

- ✓ Although the event does not immediately threaten life, result in death, or require hospitalization, if it constitutes a serious medical occurrence that places the subject at risk or necessitates medical or surgical intervention to prevent the outcomes listed above, the principal investigator or sub-investigator shall determine, based on medical and scientific justification, whether reporting as an SAE is required.

Examples include infiltrative or malignant cancer, allergic bronchospasm requiring intensive care in an emergency department or at home, and hematologic disorders or seizures that do not necessitate hospitalization.

#### 10.2.3. Recording and follow-up of Adverse Events and Serious Adverse Events

##### <Recording of Adverse Events and Serious Adverse Events>

The principal investigator or sub-investigator at the trial site shall be responsible for evaluating all records related to an AE/SAE that occur during the trial period (e.g., hospital progress notes, clinical laboratory records, diagnostic reports).

The principal investigator or sub-investigator shall document the following information concerning each AE/SAE in the source documents.

##### [Items]

- Adverse event name
- Onset date
- Severity classification (mild / moderate / severe)
- Seriousness classification (serious / non-serious)
- Causality assessment (no relationship / relationship present)
- Outcome (recovered / improved / not recovered (unchanged) / recovered with sequelae / death / unknown)
- Outcome date
- Management (whether treatment was given and its details)

The principal investigator or sub-investigator shall, based on signs, symptoms, and/or other clinical information, make every effort to identify the diagnostic term for the event. When possible, the diagnostic term—not individual signs or symptoms—should be recorded as an AE/SAE.

<Severity Assessment>

The principal investigator or sub-investigator shall classify the severity of an adverse event according to the following definitions:

Mild: Discomfort is present but does not interfere with daily activities.

Moderate: Some interference with daily activities is observed.

Severe: The subject is unable to carry out daily activities or work.

<Causality Assessment>

The principal investigator or sub-investigator shall evaluate the relationship between the investigational product and each AE/SAE and determine clinically whether a causal relationship is “present” or “absent.”

Causality determinations shall be made as follows:

✓ No relationship

The event can be clearly explained by comorbidities, medical history, concomitant medications, the known pharmacologic properties of the investigational product, or other known causes such as surgery.

✓ Relationship present (all three criteria must be satisfied)

- i. The temporal relationship between the onset of the event and the administration of the investigational product can be reasonably explained.
- ii. The event could plausibly arise from the pharmacologic action, physicochemical properties, route of administration, or other known characteristics of the investigational product or similar agents, or the principal investigator/sub-investigator acknowledges a causal relationship.
- iii. The subject’s comorbidities, medical history, concomitant drugs, or concomitant therapies are not considered contributory.

In performing the causality assessment, the principal investigator or sub-investigator shall refer to the Investigator’s Brochure, the product label, and the interview form.

In certain situations, when an SAE occurs, the principal investigator may not have obtained all information required for the initial report to the trial coordinator. Nevertheless, the principal investigator must conduct a causality assessment for each event before transmitting the SAE

data to the trial coordinator as the first report. The principal investigator or sub-investigator may revise the causality opinion in light of additional information, amend the causality assessment accordingly, and prepare an updated SAE follow-up report.

<Outcome>

The outcome of an adverse event shall be classified into one of the following categories.

- 1) Recovered: The adverse event has resolved, and the subject has returned to the pre-onset condition.
- 2) Improving: The adverse event has almost resolved, and the subject has returned to a condition close to that before onset.
- 3) Not recovered: The adverse event has not resolved, and the subject remains in the same condition as at the time of onset (unchanged).
- 4) Recovered with sequelae: The adverse event has resolved, but the subject has residual sequelae.
- 5) Death: The subject has died (regardless of causality).
- 6) Unknown: Outcome is unknown due to lack of information.

<Follow-up of Adverse Events and Serious Adverse Events>

The principal investigator or sub-investigator shall, when medically necessary or upon request from the trial coordinating physician, conduct or arrange additional examinations and/or assessments as needed to elucidate, to the greatest extent possible, the nature and/or causality of an AE or SAE. Such additional examinations may include clinical laboratory tests, ophthalmologic examinations, or consultations with other healthcare specialists.

Even if the subject does not return to normal or to the pre-investigational-product level, the principal investigator or sub-investigator may discontinue follow-up for that subject if, based on the follow-up findings, they determine that further follow-up is unnecessary and that such a decision is justified from the perspective of subject protection.

The principal investigator or sub-investigator shall document the information related to the follow-up.

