#### 2.3.1. Risk Assessment

Adverse events that may occur with administration of monteplase (genetically engineered) include retinal toxicity (retinal morphological changes, etc.), increased sub-macular

hemorrhage, macular hole, vitreous hemorrhage, anterior chamber hemorrhage, endophthalmitis, elevated intra-ocular pressure, retinal detachment, corneal opacity, progression of cataract, etc. In addition to pharmacologic effects of the drug itself, events associated with vitreous surgery or intra-ocular tamponade are also encompassed.

To minimize these risks, the trial sites for this study shall be facilities that have prior experience with sub-retinal administration of tPA preparations, and patients at high risk will be excluded by the exclusion criteria.

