#### 9.6. Safety Analyses

For the following items, the number of subjects evaluated, the number of events, and the incidence proportion will be calculated.

- Adverse events, adverse drug reactions
- Serious adverse events, serious adverse drug reactions
- Adverse events resulting in death, adverse drug reactions resulting in death
- Adverse events leading to discontinuation of the trial, adverse drug reactions leading to discontinuation of the trial

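### The causality rule contradicts itself on the drug's own pharmacology and is stricter than the standard used elsewhere in the protocol, so adverse drug reactions can be under-counted

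*Protocol*

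**What the plan says.** Section 10.2.3 records causality on a two-level scale with no intermediate category.

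- *No relationship* applies when the event has a clear explanation in comorbidities, past illness, "concomitant medications, the known pharmacologic properties of the investigational product, or other known causes such as surgery".
- *Relationship present* applies only when three criteria are all met. Criterion i is plausible timing. Criterion ii is met if "The event could plausibly arise from the pharmacologic action, physicochemical properties, route of administration, or other known characteristics of the investigational product" (agents of a like kind also count), or if the investigator acknowledges a causal relationship. Criterion iii is that the subject's comorbidities, medical history, "concomitant drugs, or concomitant therapies are not considered contributory".

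Other sections bear on the same judgement:

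- Section 2.3.1 lists increased sub-macular hemorrhage, vitreous hemorrhage and anterior chamber hemorrhage among the events that may follow administration. It then adds: "In addition to pharmacologic effects of the drug itself, events associated with vitreous surgery or intra-ocular tamponade are also encompassed".
- Section 8.4.7 has disease-related and surgery-related events, re-bleeding and vitreous hemorrhage among them, judged on whether there is a reasonable possibility of association with the trial intervention.
- Section 8.4.5 uses a reasonable possibility of a causal relationship for pregnancy-related serious events after trial completion.
- Section 10.2.1 limits a side effect to an adverse event with an established causal relationship.
- Section 9.6 tabulates "Adverse events, adverse drug reactions", and repeats the pairing for serious events, fatal events and events leading to discontinuation.

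**The concern.** The same fact, that the event follows from what the drug is known to do, is a ground for *No relationship* and also evidence for *Relationship present*. For a thrombolytic this matters most for bleeding, which is both the expected pharmacological harm and a common feature of the disease and the surgery.

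Criterion iii adds a second problem. It turns the question from whether the drug may have contributed into whether the other listed factors can be ruled out. That is a higher bar than the one in Sections 8.4.5 and 8.4.7, and re-bleeding and vitreous hemorrhage are subject to both.

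The adverse drug reaction tables rest on this classification. The trial has no control arm (Section 4.1) and no committee (Section 10.1.9), so neither a between-group comparison nor independent adjudication is available to expose misattribution. Section 10.1.14 foresees use of the data in marketing applications, so an understated reaction count could be carried forward.

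**Working it through.** No figure underlies this point, so the check is to apply the two definitions as logical rules.

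**Step 1. Role of pharmacology.** Under *No relationship*, known pharmacologic properties explain the event away. Under criterion ii, pharmacologic action supports a relationship. The protocol does not say which prevails.

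**Step 2. Work through the cases.** Assume plausible timing (criterion i) and a plausible drug mechanism (criterion ii) in each.

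| Event | *No relationship* text | *Relationship present* text | Result |
|---|---|---|---|
| Clearly explained by the drug's pharmacology; no listed factor contributory | Met | Met | Both categories |
| Clearly explained by the drug's pharmacology; a listed factor also contributory | Met | Fails on iii | Unrelated |
| Not clearly explained by any one cause; a listed factor contributory | Not met | Fails on iii | Neither category |
| Not clearly explained by any one cause; no listed factor contributory | Not met | Met | Related |

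Only the last row gives an unambiguous, sensible answer. The second row classes a drug effect as unrelated. The first and third rows have no defined outcome, and Section 10.2.3 states no default.

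**Step 3. Can the problem rows arise here?** Monteplase is a thrombolytic (Section 1.1, Rationale), and Section 2.3.1 lists three kinds of hemorrhage as possible events. Section 6.9.2.2 permits antiplatelet agents and anticoagulants, which are concomitant drugs in the sense of criterion iii and could be judged contributory to a bleed. A bleed after monteplase in a subject on an anticoagulant could therefore fall in the second or third row.

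**Step 4. Compare the thresholds.** Sections 8.4.5 and 8.4.7 ask for a reasonable possibility. Section 10.2.3 asks that the listed alternatives be non-contributory. An event in the third row could pass the first test and fails the second.

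**Step 5. Trace the consequence.** Section 9.6 has four pairs of items: all, serious, fatal, and leading to discontinuation. Each pair is one adverse event category and one adverse drug reaction category, so 4 × 2 = 8 categories. The four reaction categories depend on the causality call. The four event categories do not. Section 8.4.1 also sends every serious adverse event to the coordinating physician, in principle within 24 hours, without reference to causality.

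**The case against.** The strongest reply is that one misplaced phrase does not control the outcome. Criterion ii expressly counts pharmacologic action and route of administration and lets the investigator acknowledge causality. Investigators judge clinically and must consult the Investigator's Brochure and product label. Section 8.4.7 directs bleeding events to the lower threshold. The phrase may be no more than a drafting or translation slip, and the stated safety endpoint is adverse events, which Section 9.6 counts regardless of causality.

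Much of this stands, and it rules out three stronger readings.

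- **Bleeding would always be reported as unrelated, and the reaction count could be zero.** This is a worst case. It requires criterion ii, Section 8.4.7 and clinical judgement all to be set aside.
- **Criterion iii fails in every subject because all have AMD or RAM and all undergo vitrectomy and tamponade.** The text does not establish this. Vitrectomy and tamponade are study interventions in Table 6-1, not concomitant therapies. Surgery appears only under *No relationship*, where it must clearly explain the event. Section 8.1.1 collects the AMD or RAM diagnosis separately from comorbidities. A factor that is present has not thereby contributed.
- **Expedited reporting is compromised.** Section 10.2.3 does require a causality assessment before the first serious-event report. However, Section 10.2.4 does not tie the 7-day or 15-day decision to that classification, so this effect is possible but not shown.

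The reply does not remove the contradiction. Investigator acknowledgement satisfies criterion ii alone, and criterion iii must still be met. Section 8.4.7 sets a different standard without saying that it overrides Section 10.2.3. A possible slip is still the operative instruction.

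**Conclusion.** The point holds as an internal contradiction and a mismatch of standards. Section 10.2.3 treats the product's pharmacology as evidence in both directions, sets a stricter test than Sections 8.4.5 and 8.4.7, and leaves some mixed-cause events without a category. Followed literally, it can class drug-related events as unrelated and so understate the four adverse drug reaction categories in Section 9.6.

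The direction of the error is clear but its size is not. It depends on how many events fall in the conflicting cases and on how each investigator resolves them, and the documents give neither. The conclusion assumes that investigators apply the written rule and that the reaction tables use the Section 10.2.3 classification, as the side-effect definition in Section 10.2.1 implies. The rule should be corrected before further events are classified under it.

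**What to change.** 1. In Section 10.2.3, delete the known pharmacologic properties of the investigational product from the *No relationship* definition. This removes the contradiction.
2. Reconcile Section 10.2.3 with Sections 8.4.5 and 8.4.7: base *Relationship present* on plausible timing plus a reasonable possibility of a relationship. Keep the content of criterion iii as something to weigh in that judgement, not as a necessary condition.
3. Re-assess causality for any events already classified.

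A blanket rule that every mixed-cause event counts as related would be a policy choice and goes beyond what the contradiction requires. A single reasonable-possibility standard gives such events a category without it.

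The cost is an amendment to the appendix wording, a matching note for case report form completion, and the re-assessment. No treatment, visit or sample size changes. The downside is that somewhat more events will be counted as related.

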#### 10.2.4. Reporting of Serious Adverse Events

If an SAE occurs in this clinical trial, the principal investigator or sub-investigator shall, in accordance with the protocol's "Procedures for Handling Safety Information," promptly report the SAE to the head of the trial site, the trial coordinating physician, and the safety-information management officer. The trial coordinating physician shall immediately forward the report to the principal investigators at the other trial sites.

The principal investigator shall promptly report, for any SAE requiring follow-up, the information obtained from the follow-up to the head of the trial site, the trial coordinating physician, and the safety-information management officer. The trial coordinating physician shall also report such information to the principal investigators at the other trial sites.

<Contact for Serious Adverse Events>

- Coordinating Investigator
- Kyushu University Hospital ARO Next-Generation Medical Center Safety Information Management Unit

The trial coordinating physician shall discuss with the principal investigator whether the SAE falls under a 7-day or 15-day reporting requirement (Article 273, Paragraph 1, Items 1 and 2 of the Ordinance for Enforcement of the Pharmaceuticals and Medical Devices Act) and make a determination. If reporting is deemed necessary, the trial coordinating physician shall submit the report to the Pharmaceuticals and Medical Devices Agency (PMDA) in accordance with the “Procedures for Handling Safety Information.” The trial coordinating physician shall promptly inform all principal investigators of any adverse event reported to the PMDA. In addition, the principal investigator shall report the content to the head of the trial site.

If the principal investigator receives instructions from the head of the trial site concerning amendments to the clinical trial protocol, based on the Institutional Review Board’s opinion regarding the appropriateness of continuing the trial, the principal investigator shall comply with such instructions.

#### 10.2.5. Collection of Safety Information

The clinical trial coordinator shall independently collect information on the quality, efficacy, and safety of the investigational product. The collected information shall be handled in accordance with the “Procedures for the Handling of Safety Information,” and the necessary actions shall be taken.

## Appendix 3

### 10.3. Guidance on Contraception

#### 10.3.1. Definition of Women of Child-bearing Potential

##### Women participants of child-bearing potential

A subject is considered to be of child-bearing potential if she meets any of the following criteria:

1. She has experienced menarche.
  2. She has not undergone a sterilization procedure and has not reached a post-menopausal state.
- ✓ Post-menopausal state\* is defined as the absence of menstruation for  $\geq 12$  months in the absence of any other medical cause.
  - ✓ Serum follicle-stimulating hormone (FSH) levels may be used to confirm post-menopausal status when the subject is not receiving hormonal contraception or hormone replacement therapy (HRT). If the amenorrhea period is  $< 12$  months, confirmation by  $\geq$  two separate FSH measurements is desirable.
  - ✓ If the subject is receiving HRT and her menopausal status is uncertain, continuation of HRT during the trial is permissible only if she uses a highly effective, non-estrogenic contraceptive method. Otherwise, HRT must be discontinued prior to trial enrollment in order to verify post-menopausal status.
  - ✓ Sterilization procedures include hysterectomy, bilateral salpingectomy, and bilateral oophorectomy. For subjects with permanent infertility due to medical conditions (e.g., Müllerian agenesis, androgen insensitivity syndrome, gonadal dysgenesis), participation in the trial shall be determined by the principal investigator.

#### 10.3.2. Contraception Guidance

For female subjects of child-bearing potential, from the time of obtaining informed consent until 2 days after the last dose of the investigational product, the subject must either abstain from heterosexual intercourse or employ an effective contraceptive method such as barrier protection (condom, pessary\*, cervical cap\*), hormonal intra-uterine device, copper intra-uterine device, etc. (\*These devices are not approved or certified for use in Japan.)

## Appendix 4

### 10.4. Implementation at Partner Sites

In this clinical trial, a portion of subject visits may be conducted at partner sites that meet the following requirements. Nevertheless, the principal investigator or sub-investigator of the implementing medical institution retains responsibility for all trial-related activities performed at the partner site.

#### <Selection Criteria for Partner Medical Institutions>

A medical institution that satisfies all of items ①–③ below shall be selected as a partner medical institution and a contract shall be executed with the implementing medical institution.

- ① At least one physician permanently stationed at the institution holds the qualification of a Japanese Ophthalmological Society specialist.
- ② Medical devices used for observations during the trial period are subject to regular inspection and precision management.
- ③ An internet environment and telemedicine equipment (including a web camera of sufficient resolution to verify test results) capable of connecting with the implementing medical institution via a remote-consultation system are in place.

#### <Activities That May Be Performed When a Subject Visits a Partner Medical Institution>

- ✓ Explanation of the trial and obtaining informed consent
- ✓ Screening
- ✓ Assessments at Visit 6 (Week 2/Day 15), Visit 7 (Week 3/Day 22) and Visit 9 (Week 8/Day 57)
- ✓ Assessments at discontinuation
- ✓ Unscheduled visits (when deemed permissible by the principal investigator or sub-investigator)

#### <Receipt of Test Data from the Partner Site>

On the day of the visit, the trial site and the partner site shall be linked via the remote-consultation system, and the principal investigator or sub-investigator of the trial site shall confirm the test results performed at the partner site through a web camera.

After the remote consultation is completed, the physician at the partner site shall date and sign the printed test results and send them to the trial site as a certified copy by postal mail. In

principle, monitoring will be performed on the certified copy sent to the trial site; however, the partner site must respond to any inquiries from the monitor as necessary.

## Appendix 5

